### Data and statistical analysis

A biostatistician (AF) will oversee the blinded analyses of the data. Main comparative analyses between groups will be performed using an intention-to-treat analysis. To account for missing data, multiple imputation of missing follow-up measures, assuming missing data are missing at random and follow a multivariate normal distribution [80] will be performed as a sensitivity analysis. For continuous outcome measures, differences in mean change (baseline minus follow-up) will be compared between groups using linear regression random effects modelling adjusted for baseline values of the outcome and clustering effects of telephone coaches. Model diagnostic checks will utilise residual plots. Similar regression models for binary and ordinal outcome measures will use random effects logistic and proportional odds models, respectively. Estimates of intervention effects under hypothetical full adherence will be performed using recently developed methods based on causal modelling ideas [81] which we have successfully applied to data from our recently completed knee OA trial [79].

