### Randomisation and allocation concealment

The randomisation schedule will be prepared by the study biostatistician (AF) using a computer generated random numbers table. Randomisation will be conducted by random permuted blocks of size 6 and 12, and stratified according to treating physiotherapist so that all physiotherapists deliver approximately equal numbers in each treatment group to control for physiotherapist variation. Participants allocated to physiotherapy plus telephone coaching will be randomly allocated one of the three telephone coaches. Participants will attend their preferred physiotherapist according to geographical convenience. Consecutively numbered, sealed, opaque envelopes containing treatment group and health coach allocation will be prepared by a researcher with no other involvement in the study. The envelopes will be stored in a locked location and will be opened in sequence to reveal group allocation by a researcher not involved in recruitment.

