### Intervention providers

Thirteen physiotherapists who have at least 2 years post-graduate musculoskeletal experience and work in private clinics in metropolitan and regional Victoria will provide the physiotherapy intervention. Physiotherapists were chosen to deliver the physical activity intervention as they have expertise in exercise prescription and are key providers of structured physical activity in the community for people with knee OA. A clinical practice survey in the United Kingdom has shown that 100% of physiotherapists utilized exercise for this patient group [43].

Three registered nurses who complete training and mentoring from Health Change Australia to develop skills in providing behaviour change support will provide the telephone coaching for the study. None of the nurses will have training or experience in health behaviour change support or telephone coaching prior to involvement with this study.

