### Sample size

The primary endpoints will be change from baseline to 6 months in (i) knee pain (NRS) and (ii) physical function (WOMAC). The minimum clinically important difference to be detected in OA trials is a change in pain of 1.8 units on NRS [76] and a change in physical function on WOMAC of 6 units (out of 68) [77]. Randomisation is stratified by physiotherapist and hence no clustering effects of participants within physiotherapists need be accounted for. However, there may be clustering effects due to participants treated by the same telephone coach in the physiotherapy plus telephone coaching arm which we account for as follows: With three telephone coaches, one third of the participants in the physiotherapy plus telephone coaching arm are expected to be treated by each coach, and we assume in the sample size calculation an intra-cluster correlation of 0.05, which has been demonstrated to be conservative for patient-level outcomes across health care practices [78]. Based on combined data from our 12 month RCT in 200 people with knee OA [79] and our 12 week RCT in 76 people with knee OA who undertook a hip strengthening program [22], we assume a between-participant standard deviation of 2.2 for pain and 11.6 for WOMAC physical function, and a baseline to 6-month correlation in scores of 0.29 for pain and 0.51 for physical function. These assumptions, together with an analysis of covariance adjusted for baseline scores and for clustering, produce a sample size of 67 patients per intervention arm to achieve 80% power to detect the above differences. Allowing for a 20% attrition rate we will recruit 84 patients per arm, or 168 patients in total.

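### Randomisation is stratified by treating physiotherapist but the continuous-outcome model omits it, so its standard errors are slightly too large (minor efficiency point)

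*Protocol article*

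**What the plan says.** Under Randomisation and allocation concealment, allocation uses permuted blocks of 6 and 12 and is "stratified according to treating physiotherapist so that all physiotherapists deliver approximately equal numbers in each treatment group to control for physiotherapist variation". Intervention providers sets the number of strata: "Thirteen physiotherapists who have at least 2 years post-graduate musculoskeletal experience".

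The Sample size section then reasons: "Randomisation is stratified by physiotherapist and hence no clustering effects of participants within physiotherapists need be accounted for". For telephone coaches it takes the other course: "we assume in the sample size calculation an intra-cluster correlation of 0.05".

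Data and statistical analysis specifies, for continuous outcomes, "linear regression random effects modelling adjusted for baseline values of the outcome and clustering effects of telephone coaches". Binary and ordinal outcomes get similar random effects models. Physiotherapist appears in none of them.

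**The concern.** Stratifying on a factor and analysing by it are two halves of one device. Balancing the arms within each physiotherapist makes differences between physiotherapists largely cancel from the treatment contrast, so its true sampling error falls. A model without physiotherapist cannot see this. It counts those differences as residual noise and reports the standard error of a less efficient design.

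The error is conservative: confidence intervals slightly too wide, p-values slightly too large, and a true type I error slightly below nominal. The linear-model estimate of the treatment effect is not biased. What is at stake is that the control of physiotherapist variation sought at randomisation is only partly realised at analysis, and that the reason given for leaving the factor out could be read as a general rule.

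**Working it through.** **Inputs from the protocol article.** Sample size gives "a between-participant standard deviation of 2.2 for pain and 11.6 for WOMAC physical function", "a baseline to 6-month correlation in scores of 0.29 for pain and 0.51 for physical function", target differences of 1.8 (pain) and 6 (function), coach intra-cluster correlation 0.05 with three coaches, 67 per arm for 80% power, and 20% attrition to reach 84 per arm. There are 13 strata, or 168/13 = 12.9 randomised participants each on average.

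**Assumptions.** The significance level is not stated; two-sided 0.05 is assumed. The physiotherapist correlation ρ, as a share of residual variance after baseline adjustment, is not given; 0.02 to 0.10 is assumed.

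**1. Reproducing the sample size (function).**
- Residual variance: s² = 11.6² × (1 − 0.51²) = 134.56 × 0.7399 = 99.56.
- Design effect in the coaching arm only: 1 + (67/3 − 1) × 0.05 = 2.067.
- Variance of the difference: (99.56/67) × (1 + 2.067) = 4.557; standard error 2.135.
- Power: Φ(6/2.135 − 1.96) = 80.3%.

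Solving for the smallest n gives 67 per arm, and 67/0.8 rounds up to 84. Both match the protocol. Pain needs only 26 per arm, so function drives N.

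**2. How much physiotherapist variance the design removes.** Under simple randomisation, physiotherapist would contribute ρ × 2s²/67 = 2.972ρ to the variance of the difference. Perfect balance would remove all of it. Blocks of 6 and 12 with about 13 participants per stratum leave incomplete blocks, and dropout unbalances strata further. Simulating 13 strata, these blocks and 20% random attrition leaves about 29% of the physiotherapist contribution in the true error, so about 71% is removed.

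**3. Overstatement of the standard error.** The model without physiotherapist reports a variance of about 4.557. The true variance is 4.557 − 2.972 × 0.71 × ρ, that is 4.557 − 2.110ρ. With perfect balance it would be 4.557 − 2.972ρ. The overstatement is the square root of the reported over the true variance, minus 1.

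| Assumed ρ | True variance | SE too large by | True type I error | SE too large by, perfect balance |
|---|---|---|---|---|
| 0 | 4.557 | 0% | 0.050 | 0% |
| 0.02 | 4.515 | 0.5% | 0.049 | 0.7% |
| 0.05 | 4.452 | 1.2% | 0.047 | 1.7% |
| 0.10 | 4.346 | 2.4% | 0.045 | 3.4% |

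**4. Power for function at 67 per arm, perfect balance.** Omitting versus including physiotherapist: 80.4% versus 80.8% at ρ = 0.02, 80.7% versus 81.5% at 0.05, and 81.1% versus 82.8% at 0.10. The difference is 0.4 to 1.8 points, all of it above the planned 80%. These figures ignore the cost of estimating the extra term.

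**5. Simulation of the direction.** Ordinary least squares, coach effect left out, 4,000 runs per setting. Without physiotherapist in the model, the mean reported versus empirical standard error under no treatment effect was 1.724 versus 1.725 at ρ = 0, 1.726 versus 1.697 at 0.05, and 1.716 versus 1.602 at 0.20. Null rejection was 0.050, 0.046 and 0.041. The relative Monte Carlo error of an empirical standard error is about 1/√8000 = 1.1%, so the gap at 0.05 is suggestive and the gap at 0.20 is clear.

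**6. Thirteen fixed effects.** In the same simulation, with a treatment effect of 4.75 units, power with fixed physiotherapist effects versus none was 75.7% versus 77.7% at ρ = 0, 76.4% versus 77.3% at 0.02, 78.9% versus 78.6% at 0.05, and 80.5% versus 78.6% at 0.10. Fixed effects lose power at low ρ and pay off only from about 0.10. The random intercept was not simulated.

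**The case against.** The strongest reply is that this hardly matters. The Sample size sentence stands under that heading and is correct there: balance within physiotherapist means no design-effect inflation. The bias is conservative and cannot manufacture a positive result. The size rests on a correlation that the protocol does not give and that may be near zero. All of that stands, and it is why the point is minor.

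It might also be said that adjustment terms belong in an unseen analysis plan. That carries less weight here, because the article lists the model's adjustment terms and separately gives a reason for not accounting for physiotherapist. The omission is a stated choice.

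Several stronger readings are tempting and are not supported:

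- A reader might take the overstatement as 1/√(1 − ρ) − 1, which gives 1.0%, 2.6% and 5.4% at ρ = 0.02, 0.05 and 0.10, or 134ρ, about 3, 7 and 13 of the 134 expected completers lost. That formula assumes no coach variance and exact balance in every stratum among completers. Neither fits this protocol, and the realistic figures are less than half as large.
- A reader might infer that the trial is underpowered for function. On the protocol's own inputs it has 80.3% power, and N took no credit for a gain from physiotherapist.
- A reader might extend the same figures to the logistic and proportional odds models. Nothing was computed for those. Adding a strong covariate there also changes the odds ratio being estimated, and about 10 completers per stratum is sparse.

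**Conclusion.** The point holds as a minor efficiency finding. The continuous-outcome model leaves out the factor on which randomisation is stratified, and the stated reason is valid for the sample size but not for the analysis. Whenever physiotherapists differ in outcome, the reported standard error is too large. For function, the excess is about 0.5% to 2.4% over the assumed range of 0.02 to 0.10, and nil at zero. This rests on two-sided 0.05, coach correlation 0.05, random 20% attrition and roughly even use of the 13 physiotherapists. The direction is firm; the size is only as good as the assumed correlation. The sample size and the planned 80% power are unaffected.

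**What to change.** In Data and statistical analysis, add treating physiotherapist as a random intercept to the models for continuous outcomes, alongside baseline value and telephone-coach clustering. Prefer this to 13 fixed effects, which can cost power if physiotherapists differ little.

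In Sample size, confine the sentence to its proper scope, for example: because randomisation is stratified by physiotherapist, the sample size is not inflated for physiotherapist clustering; physiotherapist is included in the analysis model.

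The cost is one extra variance component, which may be estimated at or near zero. The planned model already has random effects, physiotherapist is known for every participant as the stratification factor, and N does not change.

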### Timeline

Ethics approval was obtained in May 2012 from the Human Research Ethics Committee of the University of Melbourne. Recruitment and training of the health coaches occurred during March – May 2012, and training of the physiotherapists was carried out in May 2012. Recruitment of participants commenced in June 2012. All participants are expected to have completed the study by end 2015.

## Discussion

The need to develop efficacious treatment approaches for knee OA that achieve long-term sustainability of improved outcomes is an important research and clinical objective. As there is no cure for OA, lifestyle behavioural change, particularly in the area of physical activity, is pivotal in knee OA management. This pragmatic RCT will provide internationally relevant, high quality Level 2 evidence of the longer-term clinical- and cost-effectiveness of a physical activity intervention involving a limited number of physiotherapy visits with and without telephone coaching. Furthermore, our inclusion of regional participants enhances the generalisability of results.

Our study will provide novel information about a clinical practice model for behaviour change support delivered by telephone that targets specific physical activity behaviours rather than a number of generic self management messages as the limited previous studies in knee OA have done. This does not diminish the importance of other aspects of self-management but rather allows interpretation of the specific effects of a physical activity intervention. The identification of feasible health care models to facilitate physical activity behaviours and improve outcomes in people with knee OA has important implications for clinical practice. Economic evaluation of treatment is also crucial in today’s health care landscape. The inclusion of this aspect in our RCT offers an additional dimension that will assist health policy makers in their decision-making regarding funding.

Telephone-delivered interventions have the potential to be adopted by the growing number of government and non-government agencies and health funds that operate telephone information and support centres. If the results of our proposed study support the clinical- and cost-effectiveness of a physiotherapy and telephone coaching intervention for knee OA, the program could be easily implemented into clinical practice using a standardised model of care. We deliberately designed the study to test an easily implementable service delivery model so as to maximise translatability. This was done by using a limited number of physiotherapy contacts consistent with the number available under the existing Medicare scheme, by using a home-based exercise program suitable to a broader public health approach, and by using a transferable telephonic coaching intervention that is inexpensive, widely accessible by and acceptable to this older patient population. Such a physical activity intervention could benefit the large number of people with knee OA and would be particularly useful for those in regional areas who may not be able to access other services.

Our study is the first RCT to investigate the effect of a telephone coaching intervention to specifically support a physiotherapist-delivered physical activity intervention on pain and function in people with knee OA. Strengths of the study design are the pragmatic nature of treatment delivery by practicing physiotherapists in community physiotherapy clinics, and by health practitioners trained in the HCA model of Health Change, as well as the reproducibility of both the physiotherapy and telephone coaching programs. These features will improve the ability to translate the findings into a range of interdisciplinary health care settings and enable future researchers to replicate the behaviour change intervention. Importantly the physical activity program is individualised with regard to the content and intensity level of the home exercises and the plan for increasing daily levels of physical activity. The study is designed so as to conform to CONSORT requirements for non-pharmacological interventions. It is adequately powered for our primary outcome measures and our recruitment strategy will result in a well-characterised sample from both metropolitan and regional areas. In addition, our study includes longer-term follow-up and primary outcomes recommended by international osteoarthritis researchers and which are of relevance to the recipients of the intervention.
